## Abstract

**Background:**

Excessive maternal pre-pregnancy and gestational weight gain are related to pregnancy- and birth outcomes. The interpregnancy time window offers a unique opportunity to intervene in order to acquire a healthy lifestyle before the start of a new pregnancy.

**Methods:**

INTER-ACT is an e-health driven multicentre randomised controlled intervention trial targeting women at high risk of pregnancy- and birth related complications. Eligible women are recruited for the study at day 2 or 3 postpartum. At week 6 postpartum, participants are randomised into the intervention or control arm of the study. The intervention focuses on weight, diet, physical activity and mental well-being, and comprises face-to-face coaching, in which behavioural change techniques are central, and use of a mobile application, which is Bluetooth-connected to a weighing scale and activity tracker. The intervention is rolled out postpartum (4 coaching sessions between week 6 and month 6) and in a new pregnancy (3 coaching sessions, one in each trimester of pregnancy); the mobile app is used throughout the two intervention phases. Data collection includes data from the medical record of the participants (pregnancy outcomes and medical history), anthropometric data (height, weight, waist- and hip circumferences, skinfold thickness and body composition by bio-electrical impedance analysis), data from the mobile app (physical activity and weight; intervention group only) and questionnaires (socio-demographics, breastfeeding, food intake, physical activity, lifestyle, psychosocial factors and process evaluation). Medical record data are collected at inclusion and at delivery of the subsequent pregnancy. All other data are collected at week 6 and month 6 postpartum and every subsequent 6 months until a new pregnancy, and in every trimester in the new pregnancy. Primary outcome is the composite endpoint score of pregnancy-induced hypertension, gestational diabetes mellitus, caesarean section, and large-for-gestational-age infant in the subsequent pregnancy.

**Discussion:**

INTER-ACT is a unique randomised controlled lifestyle intervention trial in its implementation between pregnancies and during the subsequent pregnancy, with an e-health driven approach.

**Trial registration:**

ClinicalTrials.gov Identifier: NCT02989142. Registered August 2016.

## Background

Maternal pre-pregnancy weight is related to pregnancy- and birth outcomes. An excessive weight before conception increases the risk for pregnancy- and birth related complications such as gestational diabetes mellitus (GDM), pregnancy-induced hypertension (PIH), caesarean section (CS), or a large-for-gestational age (LGA) infant [1–4]. Besides, excessive gestational weight gain (EGWG), i.e. a gestational weight gain (GWG) higher than the recommended GWG by the Institute Of Medicine (IOM) [5], is also associated with these perinatal complications [6–8]. Both the pre-pregnancy BMI and gestational weight gain (GWG) are thus considerable risk factors of pregnancy and birth complications. Between 2009 and 2014, the Flanders Study centre Perinatal Epidemiology (SPE) collected data of almost 400.000 singleton pregnancies in Flanders, Belgium, on the combined association of GWG and pre-pregnancy BMI with the prevalence of the composite outcome of pregnancy and birth complications (i.e. at least one of four perinatal outcomes PIH, GDM, CS and/or LGA infant). The prevalence of the composite perinatal outcome was 26% in women with a normal BMI and an adequate GWG; 34% in women with a normal BMI but with an excessive GWG; and 66% in women with class III obesity (BMI ≥ 40) and excessive GWG [SPE, 2016 in progress]. A Norwegian study reported similar findings. Haugen et al. [9] found that normal weight and overweight women with EGWG had an increased risk for PIH, preeclampsia, CS, high birth weight (>4500 g) and LGA infant. Moreover, women of all BMI classes and with EGWG, except underweight women, had an increased risk of more than 2 kg postpartum weight retention (PPWR) at 18 months postpartum [9]. Conversely, a more recent study from Xiong et al. reported an increased likelihood of CS in underweight or normal weight women with EGWG compared to overweight or obese women EGWG [10]. Thus, these results highlight the importance of adequate GWG in all BMI groups.

Based on the guidelines of the Institute of Medicine (IOM) [5], one in three women in Flanders, Belgium, has excessive GWG: 25% in normal pre-pregnancy BMI, 58% in pre-pregnancy overweight, and 54% in pre-pregnancy obesity [11]. Half of the women with excessive GWG do not return to their pre-pregnancy weight after delivery, resulting in a doubled risk for pregnancy- and birth related complications in the next pregnancy [12]. Retention of the excessive weight gained during pregnancy (i.e. PPWR) can result in obesity and an increased risk of chronic disease in later life [13–17]. Additionally, maternal obesity negatively affects the health of the offspring in childhood and in adulthood, by increasing the risk of obesity and the related risks of non-communicable diseases. Maternal obesity might therefore result in a vicious circle of obesity throughout generations [4, 18, 19].

Several lifestyle interventions have been implemented during pregnancy in an attempt to reduce GWG and prevent pregnancy- and birth related complications. Although these interventions showed moderate beneficial effects on GWG, they had no significant impact on pregnancy- and birth related complications [20], potentially due to the limited time window [21, 22]. Therefore, the international community of health experts has called for strategies that already intervene in the pre-conception period in order to timely acquire a healthy lifestyle and weight loss [1]. However, such strategies are still scarce [20], possibly due to unpredictability of becoming pregnant and not being linked to the health care system preconceptionally [23]. The few existing studies, though, show promising results in intervening during the preconception period [24–27]. An opportunity to overcome the barrier of reaching women in their preconception period, is to commence interventions already in the postpartum period and continuing until the next pregnancy. Such interpregnancy interventions could potentially be a unique strategy to acquire a healthy lifestyle before a subsequent pregnancy starts.

Effective lifestyle interventions for weight management among postpartum women are usually based on a combination of diet and physical activity [28–30]. Ideally, such lifestyle interventions go beyond education or advice alone and integrate behavioural change techniques such as goal setting, self-monitoring and feedback [25, 31]. Mobile applications are excellent tools to incorporate such behavioural change techniques for intervention efforts promoting a healthy lifestyle [32] that have been found effective in health behaviour change and weight loss [33].

The *inter*pregn*A*ncy *C*oaching for a healthy fu*T*ure (INTER-ACT) intervention is an e-health driven and face-to-face combined coaching program that is implemented between two pregnancies and during the subsequent pregnancy of women with an excessive GWG in the previous pregnancy. The main aim of this study is to assess the effectiveness of the INTER-ACT intervention on the composite outcomes score (GDM, PIH, CS, LGA) in the next pregnancy. This will be evaluated through a randomised controlled trial with an intervention- and control arm.

## Methods

### Study setting

INTER-ACT is a multi-centre randomised controlled trial in which six hospitals from three provinces (Leuven, Antwerp and Limburg) in the Flanders region of Belgium are involved: University Hospital Leuven, University Hospital Antwerp, GasthuisZusters Hospitals Antwerp, St-Franciscus Hospital in Heusden-Zolder, Jessa Hospital in Hasselt, and Hospital Oost-Limburg in Genk. These university, regional, or peripheral hospitals deliver each year between 900 and 2600 new-borns. Recruitment of participants takes place in these hospitals. Baseline measurements, the intervention, and follow-up measurements take place in the hospitals, private clinics, ‘Kind & Gezin’ (Child & Family) organisations, or at home, depending on the preference of the participant.

### Recruitment and eligibility criteria

Study midwives from the participating hospitals are responsible for the recruitment of participants at day 2 or 3 postpartum. To optimise recruitment, flyers and posters are placed in the waiting rooms of the participating hospitals in order to inform potential participants.

Inclusion criteria for participation in the study are the following: women aged ≥18 years; excessive gestational weight gain (above the IOM recommendations [5]) in the previous pregnancy; wish for a next pregnancy not excluded; proficiency of Dutch language; being able to use a smartphone. Exclusion criteria for participation are the following: unable or unwilling to give informed consent; no access to internet; requirement for complex medical diets; history of- or planned bariatric surgery; chronic disorders (e.g. diabetes mellitus type 1 or 2, thyroid disease, renal disease); significant psychiatric disorder; previous stillbirth. Women with twin pregnancies in either the pregnancy preceding the intervention or the subsequent pregnancy are excluded from the study. Participants can not follow other lifestyle interventions during their participation in the INTER-ACT study.

### Randomisation

After inclusion at day 2 or 3 postpartum, an electronic data capture system (CASTOR) will randomise participants in the intervention or control group. Randomisation is revealed at week 6 postpartum. Due to the nature of the intervention (i.e. coaching sessions and use of mobile app, weighing scale and activity tracker), no blinding is involved in this study.

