### Outcomes

In this RCT, we aim to evaluate a composite outcome as primary outcome, of which at least one of the following outcomes occurs in the subsequent pregnancy:Pregnancy-induced hypertension (PIH): new-onset elevations of blood pressure (systolic blood pressure > 140 mmHg and diastolic blood pressure >90 mmHg) after 20 weeks of gestation without significant proteinuria [35].Gestational diabetes mellitus (GDM): is defined as any degree of glucose intolerance with onset or first recognition during pregnancy [36]. GDM is diagnosed at 24–28 weeks of gestation with the two steps screening strategy which consists of a 50 g glucose challenge test (GCT) and a 2-h 75 g oral glucose tolerance test (OGTT). GDM is diagnosed upon an abnormal GCT (≥ 140 mg/dl) followed by an abnormal OGTT (≥ 153 mg/dl) based on the VDV-VVOG-Domus Medica consensus 2012 and IADPSG criteria [37].Caesarean section (CS): surgical procedure in which a foetus is delivered through an incision in the mother’s abdomen and uterus.Large-for-gestational-age baby (LGA): birth weight >90^th^ percentile on Flemish sex- and parity-adjusted growth charts [38].

Secondary outcomes are the following:Maternal weightBody compositionBlood pressureBreastfeedingFood intakePhysical activityLifestyle behaviourQuality of lifeMental wellbeing

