### Data collection

#### Time of data collection

Clinical data (i.e. medical record data and anthropometric data) and non-clinical data (i.e. data from the mobile app and self-administered questionnaires) are collected at day 2–3, week 6, and month 6 postpartum, every subsequent 6 months until the next pregnancy, and at week <15, 20, and 35 during the next pregnancy (Fig. 1). Deviation of 2 weeks before or after the planned time point is allowed.

At inclusion (day 2 or 3 postpartum) and at the end of the subsequent pregnancy, data will be collected from the medical record. During each coaching session, data from the mobile app will be collected (intervention group only). During all measurement moments (except day 2/3 and delivery of the next pregnancy) anthropometric data and self-administered questionnaires are collected (Fig. 1).

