### Data management

The data from the questionnaires, the anthropometric data and medical record will be entered and stored in a full Good Clinical Practice (GCP) compliant Electronic Data Capture system, i.e. the CASTOR electronic case report form (eCRF). The data of the mobile application (i.e. physical activity from the activity tracker, weight evolution and mood status) of the participants can be retrieved from the secured website of INTER-ACT, of which only the research team and the participant can have access. Length and weight after delivery will be transferred from the eCRF to the mobile application in order to be able to calculate BMI and show weight curves. In case of no database access, data will be entered on paper CRF and subsequently entered into the data system when access is possible.

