### Statistics

All analyses will be carried out using the intention-to-treat principle with data from all participants enrolled in the study. The statistical software SAS version 9.4 will be used. Descriptive statistics for baseline values in the two arms will be presented. There will be no tests of statistical significance or confidence intervals for differences between the two arms, as these are randomised groups. The drop-out rate will be assessed and compared between the two arms. The composite endpoint consists of occurrence of at least one of the following four major pregnancy and birth related complications, at time of next pregnancy: PIH, GDM, CS, and LGA. The rate of the composite endpoint will be calculated and 95% confidence intervals provided in intervention and control arm: 1) in all included patients (intent-to-treat), 2) in all patients completed a next pregnancy. If drop-out rates, reason for drop-out, next pregnancy rates differ between the intervention arm and control arm, the rate of the composite endpoint in patients with a next pregnancy has to be interpreted carefully.

A full statistical analysis plan will be written by the trial statistician prior to any analysis being undertaken. We will report data in line with the Consolidated Standards of Reporting Trials (CONSORT) 2010 Statement [54] and a *P*-values <0.05 will be considered statistically significant.

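### The plan rules out all blinding for a reason that covers only participants and coaches, so as worded it also rules out masked outcome derivation and analysis, where masking is feasible

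*Protocol article*

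**What the plan says.** The Randomisation section states that "no blinding is involved in this study" and gives one reason: "Due to the nature of the intervention (i.e. coaching sessions and use of mobile app, weighing scale and activity tracker"). The same section says "Randomisation is revealed at week 6 postpartum". No other section narrows the sentence or describes masked extraction, masked classification or a masked analyst.

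The primary endpoint is a composite: "The composite endpoint consists of occurrence of at least one of the following four major pregnancy and birth related complications", namely PIH, GDM, caesarean section (CS) and a large-for-gestational-age infant (LGA) in the next pregnancy. Its data come from routine records: "at the end of the subsequent pregnancy, data will be collected from the medical record" (Time of data collection). They are stored in "the CASTOR electronic case report form (eCRF") (Data management), and the Randomisation section names CASTOR as the system that also allocates the women. The Statistics section says that the trial statistician will write a full SAP before any analysis.

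**The concern.** The reason given is narrower than the rule it supports. Coaching sessions, an app, a scale and a tracker cannot be hidden from the woman who uses them or from the coach. They do not stop someone from deriving the composite from recorded values without the allocation, or a statistician from working with coded arms. Because the rule is stated positively and without limit, it is more than a detail left to a fuller document.

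At stake is differential classification of the primary endpoint. The arm is known from week 6 postpartum, before any endpoint event can occur. Under a rule of at least one component, one judgement can turn a non-event into an event, or the reverse, in a woman with no other component. If such judgements lean towards the arm that staff expect to do better, the comparison is biased in that direction, and analysis choices made with the arms visible could add to this.

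**Working it through.** **1. Who the stated reason covers**

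| Role | Does the stated reason prevent masking? |
|---|---|
| Participant | Yes: she receives the coaching and devices |
| Coach | Yes: delivers the coaching and sees the app data |
| Person entering subsequent-pregnancy data | Not in itself; the role is not identified in the article |
| Derivation of the composite | No: it can be programmed from recorded values |
| Statistician | No: arms can be coded |

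**2. Where judgement can enter, by component (Outcomes section)**

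- PIH: defined by "new-onset elevations of blood pressure" after 20 weeks, with pressure thresholds. The article does not say how many readings, or from which setting, count. Blood pressure is also measured at study visits (Anthropometric data), so there is more than one source of readings. For proteinuria, the Medical record data section gives a figure, above 300 mg/24 h, so that part leaves less room.
- GDM: the cut-offs are numeric (glucose challenge test at least 140 mg/dl, then oral glucose tolerance test at least 153 mg/dl). A broader general definition precedes them, so judgement remains mainly for a diagnosis made outside the two-step route.
- CS: "surgical procedure in which a foetus is delivered through an incision". This is a recorded fact with little room in extraction.
- LGA: birth weight above the 90th percentile of a growth chart, again with little room.

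The exposed women are therefore mainly those whose only component would be PIH or an atypically diagnosed GDM, together with those with incomplete records.

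**3. The plan's own figure**

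Inputs from Sample size: 42% and 30%, power 80%, level 0.05 (taken as two-sided). With mean rate 0.36:

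n = [1.96 × √(2 × 0.36 × 0.64) + 0.8416 × √(0.42 × 0.58 + 0.30 × 0.70)]² / 0.12² = [1.96 × 0.6788 + 0.8416 × 0.6735]² / 0.0144 = 250 per arm.

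This reproduces the stated 250. Masking would not change it.

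**4. Illustration of scale (the bias is an assumption, not a figure from the documents)**

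Take a true rate of 42% in both arms, n = 250 per arm, and a classification shift b that lowers the observed rate in the intervention arm to p₂ = 0.42 − b. Let p̄ be the mean of 0.42 and p₂, and let

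- SE₀ = √(2p̄(1 − p̄)/250)
- SE₁ = √((0.42 × 0.58 + p₂(1 − p₂))/250)

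Chance of a significant result favouring the intervention = Φ((b − 1.96 SE₀)/SE₁). Chance of one favouring control = Φ((−b − 1.96 SE₀)/SE₁).

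| b | Women of 250 | Favours intervention | Two-sided error |
|---|---|---|---|
| 0 | 0 | 2.5% | 5.0% |
| 1 point | 2.5 | 4.2% | 5.6% |
| 2 points | 5 | 6.6% | 7.4% |
| 3 points | 7.5 | 10.1% | 10.5% |

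For b = 0.02: p̄ = 0.41 and SE₀ ≈ SE₁ ≈ 0.0440, so (0.02 − 0.0862)/0.0440 = −1.51 and Φ = 0.066.

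**5. How plausible is such a shift?**

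Two points is 0.02/0.42, about 5% of all events in the arm. If the movable cases were only women with PIH and no other component, and these were an assumed 3% to 8% of women (the documents give no such rate), a 2-point shift needs 0.02/0.03 = 67% to 0.02/0.08 = 25% of them misclassified, all in one direction and one arm. A 3-point shift needs 100% to 38%. The upper rows of the table are therefore demanding unless GDM diagnoses and incomplete records add to the movable cases.

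**The case against.** The strongest reply is that the sentence may simply be a loose way of saying that the trial is open-label. It stands under Randomisation, its reason concerns coaching and devices, and the article condenses a fuller protocol. Masking of the statistician in particular is often set in a SAP, and the article promises one before any analysis. The composite is already defined, most components are numeric or recorded facts, and app data already sit on a separate secured website.

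Much of this stands, and it limits the size of the point. It does not remove it: the sentence as printed has no limit, and a later document that masked the analyst would contradict it.

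Two stronger readings are tempting. A reader might infer that the endpoint is in fact extracted and classified by people who know the arm. The documents do not say who does this or what they see. A reader might also infer that, because CASTOR both randomises and stores outcomes, whoever enters outcomes sees the arm. The article says nothing about user rights or what is displayed, so this is not supported either.

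It is also fair to say that a separate data enterer at every site is not shown to be available. The article names recruiting midwives and trained coaches, but does not say whether they are different people. Hiding a field may not fully mask local staff, since coaching can take place in the same hospital.

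**Conclusion.** The point holds in a limited form. The blanket sentence goes further than its reason and, as worded, rules out masked derivation and masked analysis, both of which are feasible here. The exposure is confined mainly to PIH classification, GDM diagnosed outside the two-step route, incomplete records and analysis choices, and a judgement changes the composite only in a woman with no other component.

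The calculation shows how sensitive the result would be to a small differential shift; it does not estimate bias in this trial. It rests on an assumed shift in one direction and one arm, a true rate of 42% in both arms and 250 deliveries per arm. This is an improvement to consider, and the sample size is unaffected.

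**What to change.** Replace the blanket sentence with wording on these lines:

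*Participants and coaches are not masked. Subsequent-pregnancy data are entered as raw values (blood pressure with gestational week, proteinuria, GCT and OGTT values, mode of delivery, birth weight), with the allocation field hidden and, where existing staff allow, by someone other than the woman's coach. The composite is derived from these values by a fixed program without the allocation. The trial statistician works with coded arms until the SAP is signed and the composite is locked.*

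The cost is protocol wording, some user-rights work in the data system and some extra data entry for the raw values. The change does not remove the influence of unmasked clinicians on the decision for CS or on testing, and the report should say so.

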### Intervention

The intervention consists of two intervention phases. The first intervention phase starts at 6 weeks postpartum and lasts until 6 months postpartum. The second intervention phase starts before the 15^th^ week of the next pregnancy and lasts until the 35^th^ week of the pregnancy. A deviation of 2 weeks before or after the planned time point is allowed. Both intervention phases comprise face-to-face coaching and use of a mobile application. Between the two intervention phases, participants in the intervention group receive motivational reminders by e-mail every 3 months.

#### Face-to-face coaching

During both intervention periods, women receive face-to-face coaching sessions: four during the interpregnancy period and three during the next pregnancy (Fig. 1). Coaches trained in motivational interviewing and behavioural change techniques conduct the coaching sessions. During the coaching sessions, the participant is sensitised about the benefits of a healthy lifestyle and the adoption of a healthy lifestyle is stimulated. SMART (Specific, Measurable, Achievable, Relevant and Time specific) goal setting, action planning and reinforcement support the adoption of a healthy lifestyle. Besides, potential barriers to achieving goals or a healthy lifestyle are identified as well as individually tailored solutions to overcome these barriers. The data from the mobile app, i.e. the evolution of body weight, physical activity and mental well-being, support these coaching sessions.

